# STUDY DESIGN

## TYPE OF STUDY

This is a prospective, randomised, open-label, single-centre standard care study. Randomisation will be carried out according to the modified Zelen method.

## STUDY DURATION

The total study duration is 18 months. The inclusion period is 12 months. The length of participation in the study for each patient will be 6 months.

## RANDOMISATION ARM ALLOCATION

The randomisation list will be drawn up using blocks of varying sizes. The list and size of the blocks will not be communicated to the investigators. Concealed allocation will take place using a computerised randomisation system.

## EXPERIMENTAL DESIGN

### Randomised trial

Two patient groups will be studied: the investigational group which will receive text messages (G2) and the control group which will receive standard management (G1).

The randomised controlled trial is the reference method for assessing treatment. Randomisation is the only method which yields comparable groups for known and unknown prognostic factors and limits selection bias.

The comparator will correspond to the patients’ standard management by their diabetes specialist.

### Rationale for the modified Zelen design:

The primary endpoint is HbA1c level at 6 months. Changes in this level are related to patient compliance. One of the secondary endpoints (satisfaction, quality of life) is a patient-reported endpoint which, by definition, is totally subjective. A recent study showed that, in the absence of blinding, the treatment effect is overestimated for randomised trials with a subjective endpoint (Wood L, BMJ 2008). In order to limit bias related to the absence of blinding, we propose to use a modified Zelen design.

We will use the Zelen method while obtaining agreement to take part in two stages. All eligible patients and their parents will initially be invited to take part in a cohort study aiming to assess changes in diabetes control over a 6-month period. An information leaflet (IL1) on the study objectives and procedures will be given to the parents and young patients. Patients will be informed that they may choose not to take part in the study. Secondly, still during the first appointment, after the randomisation step, adolescents randomised to the interventional group, and their parents, will be invited to take part in a study assessing text messaging intervention. A second information leaflet (IL2) on the study objectives and text messaging intervention procedures will be given to the parents and young patients. Patients will be informed that they may choose not to take part in this study.

This method makes it possible to avoid the risks of bias due to the absence of blinding. In a conventional randomised trial, patients assigned to the control arm may modify their behaviour as they know they will not receive text messaging support.

This design is acceptable in this context for several reasons: The procedure for obtaining consent in two stages has already been used to assess rehabilitation, and several ethics committees have approved its use in this context (Quilty *et al*., 2003, Rannou, PHRC National in press, Forestier R, ARD 2009).

From a methodological perspective, the limitations of the Zelen design correspond to contamination risks due to refusal of intervention. In our study, the contamination risk should not be high in view of:

- The absence of risk related to intervention

- The short intervention time-frame

- Contamination risk in the standard management group is very unlikely as this text messaging intervention is not currently proposed outside the scope of this study.

### Procedures for limiting missing data

No or very few patients will be “lost to follow-up”, in view of their age and their usual obligations in terms of medical follow-up. The number of missing data should be very low.

## ENDPOINTS

### Primary endpoint

HbA1c, quantifying blood glucose control, will be used to define the primary endpoint. An improvement in blood glucose control is defined as a 1% reduction in HbA1c at 6 months.

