# **SYNOPSIS**

| Title | Impact of Mobile Phone Short Text Messages on the Glycaemic Control of Adolescents With Poorly Controlled Type 1 Diabetes. |
| --- | --- |
| Coordinating Investigator | [name] |
| Investigating Centre | Paediatric Endocrinology Department, Hôpital Necker |
| Type of standard care assessed | Text message sent to adolescents reminding them to administer their insulin injection |
| Study duration | 1 year |
| Patient follow-up | 6 months |
| Target population | Adolescents aged between 12 and 20 years inclusive, with inadequately controlled type 1 diabetes |
| Study objective | The primary objective of this study is to assess whether intervention by sending a text message to adolescents with inadequately controlled type 1 diabetes reduces the HbA1c level by 1% at 6 months.  Secondary objectives:   - Measurement of compliance at 3 and 6 months. - Measurement of quality of life at 3 and 6 months - Changes in HbA1c level at 3 months |
| Methodology | Prospective randomised single-centre interventional standard care study. Randomisation as per the Zelen method. |
| Planned number of centres | 1 |
| Planned number of patients | 100 subjects will be included  50 patients in group G1 = Standard management  50 patients in group G2 = Text messaging |
| Selection criteria | Inclusion criteria:   - aged between 12 and 20 years inclusive - type 1 diabetes - diagnosed more than 6 months previously - HbA1c level at enrolment greater than or equal to 8.5% - for minors: no objection by a person with parental authority - for adults: no objection by the patient - previous medical examination (Art. L.1121-11 of the French Public Health Code) - able to be followed up for 6 months following inclusion. - patient registered with or covered by a health insurance scheme - adolescents with a mobile phone able to receive text messages (SMS)   Exclusion criteria:   - aged under 12 years or over 21 years - with a HbA1C level at enrolment < 8.5%. - pregnancy - serious psychiatric comorbidity, such as serious personality disorder or psychosis. - patient and/or parents unable to understand or speak French, hence unable to understand the non-objection form. |
| Criteria for premature withdrawal | - withdrawal of consent - decision by the patient or parents to no longer be followed up in the study |

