| Study implementation | Adolescents with type 1 diabetes whose current glycated haemoglobin level is greater than or equal to 8.5% are included and randomised to two groups, then followed up for 6 months:   - patients with standard follow-up (G1), - patients with standard follow-up and receiving text messages (SMS) (G2).   V0- Inclusion visit   - Verification of eligibility criteria - Invitation to take part in the study. - Collection of the non-objection form for participation in a cohort on compliance (IL1) - Randomisation. - Only adolescents randomised to group G2 are informed that they will receive text messages (SMS) (Zelen method). - Collection of the non-objection form for participation in the text messaging (SMS) study if the patient is randomised to the investigational arm (IL2) - Inclusion - Clinical examination - Blood sample: assay of HbA1c level - Completion of quality of life questionnaire - Completion of inclusion form   M3 – 3-month visit   - Clinical examination - Blood samples for laboratory work-up (assay of HbA1c level) - Completion of M3 follow-up form - Completion of quality of life questionnaire - Collection of blood glucose monitoring diary and distribution of a second diary   M6 – 6-month visit:   - Clinical examination - Blood samples for laboratory work-up (assay of HbA1c level) - Completion of M6 follow-up form. - Collection of capillary blood glucose diary distributed at M3. - Completion of quality of life questionnaire - Satisfaction survey for patients randomised to the text messaging arm   Text messaging characteristics:   - A text message will be sent every day. - At the usual insulin injection times based on the patient’s personal therapeutic regimen. - Example of message content:   *“Remember to administer your slow-acting insulin injection.”*  *“You are about to have your meal; remember to administer your rapid-acting insulin injection (or bolus - if a pump is used).”*  *“Remember to administer your mixed insulin injection.”* |
| Primary and secondary endpoints | Primary endpoint   - HbA1c level at 6 months   Secondary endpoints   - HbA1c level at 3 months - Measurement of compliance at M3 and M6: blood glucose monitoring diary - Inclusion, M3 and M6 quality of life questionnaire. - Satisfaction survey for patients randomised to the text messaging arm |

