## PRIMARY OBJECTIVE

The primary objective of this study is to assess whether intervention by sending a text message to adolescents with inadequately controlled type 1 diabetes, over a 6-month period, significantly reduces the HbA1c level.

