### Secondary endpoints

The secondary endpoints are as follows:

- Improvement in blood glucose control at 3 months
- Measurement of compliance: by assessing the capillary blood glucose diary, at 3 months and at the end of the study.
- Measurement of quality of life among the adolescents: anonymous self-administered questionnaire distributed, at inclusion, at 3 months and at the end of the study (PedsQL questionnaire version 4.0).
- Satisfaction survey after 6 months of participation in the study.

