# STATISTICAL CONSIDERATIONS

## Rationale for the sample size

Based on the results of the Hvidore study (Holl RW Eur J Pediatr 2003), we assume that the HbA1c level will follow a normal distribution, with a standard deviation of 1.6. The sample size necessary was calculated to evidence a difference in HbA1c level between the 2 “standard management” and “text messaging” groups of at least 1% after a 6-month follow-up period. Taking into account a type I error of 5% and 80% power, 41 subjects per group, i.e. 82 subjects in total, will need to be included and randomised.

To take into account a potential rate of refusal to take part in the “text messaging” arm, of approximately 10%, the sample size necessary was increased by 20%, i.e. 50 subjects per group, 100 subjects in total (Zelen, Stat med 1990).

Children who withdraw their consent, after being randomised to the “text messaging” arm will be followed up under the same conditions as those in the “standard management” group.

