## Description of planned statistical methods, including the planned interim analysis schedule

The statistical analysis will be carried out using SAS software, under the supervision of [name] (Paris Centre CRU - Cochin-Necker). The statistical analysis will be carried out at the end of data collection, data entry and data consistency checks.

A descriptive analysis of the characteristics of the children included in each group will be performed first of all. Quantitative data are expressed as the mean ± standard deviation or median and range, and as the sample size and percentage for qualitative data.

The primary endpoint and secondary endpoints will be analysed on an intention-to-treat basis, i.e. all randomised patients will be analysed in their randomisation arm, irrespective of the intervention received. All tests used will be two-sided, with a 5% significance level.

*Main analysis*

The HbA1c level after the 6-month follow-up period will be compared between the “text messaging” and control groups using Student’s *t*-test.

*Secondary analyses*

The HbA1c level after the 3-month follow-up period will be compared between the “text messaging” and control groups using Student’s *t*-test.

For all secondary endpoints, satisfaction and compliance, two means will be compared using Student’s *t*-test or a Wilcoxon test if necessary. The percentages will be compared using the Pearson Chi-2 test or Fisher’s exact method, if necessary.

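### The primary endpoint section and the synopsis objective rest on a 1% HbA1c reduction, but the trial is sized and tested for a between-arm difference in 6-month HbA1c level against zero

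*Protocol*

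**What the plan says.** The protocol states its primary question in several forms.

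- **Section 4.5.1 (Primary endpoint):** HbA1c is to be used to define the endpoint, and the only definition that follows is "An improvement in blood glucose control is defined as a 1% reduction in HbA1c at 6 months".
- **Synopsis, study objective:** whether messaging "reduces the HbA1c level by 1% at 6 months".
- **Section 2.2 (Primary objective):** whether messaging, "over a 6-month period, significantly reduces the HbA1c level". There is no threshold.
- **Synopsis, endpoint list:** "HbA1c level at 6 months". Section 4.4.2 names the same endpoint when it justifies the Zelen design.
- **Section 12.1 (sample size):** a difference between the "groups of at least 1% after a 6-month follow-up period" is the difference to be detected, with SD 1.6.
- **Section 12.2 (main analysis):** Student's t-test on the 6-month HbA1c level between arms. "All tests used will be two-sided, with a 5% significance level".

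The 3-month endpoint varies in the same way. Section 4.5.2 lists "Improvement in blood glucose control at 3 months", the synopsis objectives speak of changes in HbA1c, and the synopsis endpoint list and section 12.2 use the HbA1c level.

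**The concern.** Section 4.5.1 is where a reader looks for the primary endpoint, and its only definition is one that no planned analysis uses. The definition is also incomplete. It does not say whether the reduction applies to a patient or to a group mean, or whether it is measured from baseline or against control.

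Two things are at stake. First, the synopsis objective promises an answer to whether HbA1c falls by 1%, and the planned test addresses only whether the difference is zero. A significant result could be reported as meeting an objective that it does not establish. Second, two descriptions of the primary outcome stand in one protocol for an open-label trial. Which one governs should be settled before results are seen, and a later analysis document cannot settle a contradiction within the protocol itself.

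**Working it through.** **Inputs**

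- Difference to detect: 1 HbA1c percentage point (12.1)
- SD of the HbA1c level: 1.6 (12.1)
- Error rates: "Taking into account a type I error of 5% and 80% power, 41 subjects per group" (12.1); tests two-sided (12.2)
- Final size: 50 per group after inflation (12.1)

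**Step 1. Reproduce the sample size.**
n per group = 2 × [SD × (z₀.₉₇₅ + z₀.₈₀) / difference]² = 2 × [1.6 × (1.960 + 0.842) / 1]² = 40.2, rounded up to 41. This matches the protocol. The increase of 20% gives 41 × 1.2 = 49.2, taken as 50. The calculation is therefore for a two-sided comparison of mean 6-month levels, with zero as the null and 1 point as the alternative. It agrees with section 12.2.

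**Step 2. Smallest observed difference that is significant.**
Standard error at 50 per arm = 1.6 × √(2/50) = 0.320.
Critical difference = t₀.₉₇₅,₉₈ × 0.320 = 1.984 × 0.320 = 0.635, about 0.64 points. At 41 per arm it is 0.70.

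**Step 3. What a positive result would show.**
The 95% CI is the observed difference ± 0.635.

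- Observed 0.64: about 0.00 to 1.27
- Observed 1.00: about 0.37 to 1.63

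Both intervals extend well below 1. If the true difference is exactly 1.0, the share of significant results with an observed difference below 1 is (normal approximation) [Φ(0) − Φ((0.635 − 1)/0.32)] / [1 − Φ((0.635 − 1)/0.32)] = (0.500 − 0.127) / 0.873 = 43%.

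**Step 4. Set the statements beside the analysis.**

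| Place | Quantity | Matches the planned test? |
| --- | --- | --- |
| Synopsis endpoint list; 4.4.2 | HbA1c level at 6 months | Yes |
| 2.2 | Significant reduction | Yes |
| 12.1 | 1 point as planning difference | Yes |
| Synopsis objective | Reduction by 1% | No |
| 4.5.1 | Improvement, defined as a 1% reduction | No |
| 4.5.2 (3 months) | Improvement | No; the level is tested |

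**Step 5. What baseline adjustment would add.**
HbA1c is measured at inclusion (5.1, 5.2). Adjusting for it multiplies the standard error by about √(1 − r²), where r is the correlation between baseline and 6-month values among enrolled patients. The protocol gives no r. For an assumed r of 0.3 to 0.7 the factor is √0.91 = 0.95 to √0.51 = 0.71.

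**The case against.** The strongest reply is that the tested endpoint is stated plainly. Section 4.4.2 and the synopsis endpoint list both name the 6-month HbA1c level, section 12.2 fixes one main analysis of it, and section 12.1 sizes that analysis correctly. On this view the 1% in 4.5.1 is only the planning difference stated in the wrong place. Reaching significance below the planning difference is a normal property of a superiority test. All of this stands as a defence of the test and the sample size. It does not repair 4.5.1 or the synopsis objective, which say something else.

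Three stronger readings are tempting, and the documents do not support them.

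- **A reader might infer that 4.5.1 defines a within-patient responder event.** It mentions neither individual patients nor change from baseline. That section 5.1 has the endpoint assessed at inclusion makes the reading possible but does not establish it. No responder test of HbA1c is specified as the main analysis; the tests of percentages in 12.2 fall under secondary analyses.
- **A reader might infer that regression to the mean, from enrolling at HbA1c of 8.5% or more, undermines the result.** The planned analysis compares randomised arms, and regression to the mean affects both equally.
- **A reader might infer a definite loss of power under a responder endpoint.** Any figure depends on the spread of change and on the baseline correlation, and the protocol gives neither. What can be said is that no responder or 1%-margin analysis was sized.

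**Conclusion.** The endpoint wording in 4.5.1 and the objective in the synopsis are wrong as written, because they contradict the endpoint that the protocol names elsewhere, sizes and tests. The wording of the 3-month endpoint in 4.5.2 has the same fault. The sample size and the t-test are sound.

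The gap is measurable. Under the protocol's SD of 1.6 and 50 analysed per arm, a difference of about 0.64 points is already significant, so a positive trial would support section 2.2 but would not establish the synopsis objective of a 1% reduction. Fewer analysed patients raise that threshold somewhat (0.70 at 41 per arm) without changing the conclusion.

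The severity is moderate: the contradiction concerns the primary endpoint, but the main analysis is fixed and conduct is unaffected. Baseline adjustment is a separate, free improvement; the contradiction does not depend on it.

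**What to change.** 1. **4.5.1:** state one primary endpoint, HbA1c level (%) at 6 months. Define the treatment effect as the between-arm difference in means, adjusted for baseline HbA1c. Name the matching baseline-adjusted comparison in 12.2 in place of the unadjusted t-test.
2. **4.5.1:** remove the 1% definition, or move it to the secondary endpoints as a descriptive responder rate by arm, labelled as such and fully defined (per patient, from baseline, in absolute percentage points).
3. **Synopsis objective:** reword to agree with 2.2.
4. **12.1:** say that 1% is the planning difference only. In 12.2, commit to reporting the 95% CI for the between-arm difference, so that readers can judge it against 1 point.
5. **4.5.2 and the synopsis secondary objectives:** define the 3-month endpoint as HbA1c level at M3.

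If a 1-point margin or a responder endpoint is what the sponsor really intends, the main analysis and the sample size must be redone for it.

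The cost is wording in the synopsis, 4.5.1, 4.5.2, 12.1 and 12.2. No visit, sample or data item is added, since baseline HbA1c is already collected, and the planned 100 patients need not change.

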### Secondary endpoints

The secondary endpoints are as follows:

- Improvement in blood glucose control at 3 months
- Measurement of compliance: by assessing the capillary blood glucose diary, at 3 months and at the end of the study.
- Measurement of quality of life among the adolescents: anonymous self-administered questionnaire distributed, at inclusion, at 3 months and at the end of the study (PedsQL questionnaire version 4.0).
- Satisfaction survey after 6 months of participation in the study.

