| Statistical analysis | Analysis of the primary endpoint: comparison of HbA1c level at 6 months between patients having received text messages and patients not having received reminder text messages.  Analysis of the secondary endpoints: comparison of HbA1c level at 3 months, compliance and quality of life between patients having received text messages and patients not having received reminder text messages, analysis of the satisfaction survey. |

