# DATA MANAGEMENT

## Right of access to data and source documents

### Access to data and confidentiality

The administrator ensures that the protocol and information leaflet intended for patients included in the study or their representatives stipulate that the investigators shall allow access to the documents and personal data strictly required for monitoring, quality control and audits of a study aiming to assess standard care, by personnel individually appointed for this purpose by the study administrator. The administrator also ensures that each person taking part in the study has not objected to allowing access to their personal data.

These activities must comply with strict confidentiality regulations. Personnel thus appointed for these purposes are bound by professional secrecy, notably under the conditions defined in Articles 226-13 and 226-14 of the French Penal Code, in the same way as the investigators themselves.

During and at the end of the study, data collected on the participants and transferred to the administrator by the investigators (or any other study personnel) shall be coded. Under no circumstances shall these data clearly display the names or addresses of the persons concerned, or any other identifiable information. Data will be collected on each patient from the case report form. Patients will be allocated a study-specific code number, indicating the centre, order of inclusion and the patients’ initials (surname and first name).

Telephone contact details for all patients will be forwarded to a call centre. The study inclusion number, telephone number (without the patient’s name and address) together with the text messaging dates and times will be recorded on a secure web platform, separate from the case report form, allowing the text messages to be scheduled within the time-frames stipulated by the protocol. This platform will be accessed via a login and password. The information given to the service provider, namely the patient’s telephone contact details and inclusion number, will not be stored by the service provider but will be destroyed after the last text message has been sent.

The study database will only contain medical data (taken from the patient’s medical record at inclusion, at 3 months and at 6 months).

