Appendix 4: 3 MONTH FOLLOW-UP DATA COLLECTION FORM

Impact of Mobile Phone Short Text Messages on the Glycaemic Control of Adolescents With Poorly Controlled Type 1 Diabetes.

Appointment date: …/.../... (dd/mm/yyyy)

1) Study data: to be completed by the coordinator

Patient code: |__|__|__| |__|__|__| |__| |__|

2) HbA1c level

Sampling date for second HbA1c level: …/.../... (dd/mm/yyyy)

Result: ….... %

3) Adverse event to be notified, comments:

…....................................................................................................................................................................

…....................................................................................................................................................................

4) Collection of the capillary blood glucose diary: yes no

Percentage of insulin injections recorded _ _%

5) Distribution and collection of the quality of life questionnaire: yes no

6) Distribution of the second capillary blood glucose diary: yes no

7) If the patient has been randomised to the text messaging arm:

Did s/he send a “STOP” text message yes no

If “yes”, date on which this text message was sent: …/.../... (dd/mm/yyyy)

If this is the case, in a single sentence, indicate the main reason given by the adolescent: ……………………………………………………………………….

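### Section 4.5.2 calls the quality-of-life questionnaire anonymous, which as written conflicts with comparing it by randomised arm; no link from answers to arm or visit is stated

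*Protocol*

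**What the plan says.** Section 4.5.2 lists quality of life (PedsQL version 4.0) as a secondary endpoint, measured by an "anonymous self-administered questionnaire distributed, at inclusion, at 3 months and at the end of the study". Section 2.3 makes the same three measurements a secondary objective.

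The analysis text needs those answers to be attributable. The Synopsis announces a "comparison of HbA1c level at 3 months, compliance and quality of life between patients having received text messages" and patients who did not receive them. Section 12.2 puts primary and secondary endpoints on an intention-to-treat basis: "all randomised patients will be analysed in their randomisation arm, irrespective of the intervention received".

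On data handling, Section 9.1.1 states that "data collected on the participants and transferred to the administrator by the investigators (or any other study personnel) shall be coded". It adds: "Patients will be allocated a study-specific code number, indicating the centre, order of inclusion" and initials. The same section describes the study database as holding only medical data drawn from the patient's record.

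On the forms, Appendix 4 (item 5) has "Distribution and collection of the quality of life questionnaire: yes no", and Appendix 5 has an equivalent line. Both forms carry the patient code. Appendix 3, the inclusion form, has no quality-of-life item, although the Synopsis and Section 5.2 schedule the questionnaire at inclusion. The PedsQL itself is not among the listed appendices.

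**The concern.** A comparison by randomised arm needs each answer sheet to carry at least its arm and its visit. A sheet that is anonymous in the strict sense carries neither. The Protocol has a separate term, coded, for data that are confidential but still attributable, and Section 4.5.2 does not use it for this instrument.

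What is at stake is a named secondary objective. Section 4.4.2 also defends the modified Zelen design partly on the ground that satisfaction and quality of life are subjective, patient-reported endpoints vulnerable to the lack of blinding. Collecting one of them in a way that could prevent comparison by arm would undercut that argument.

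This is a collection rule, so a statistical analysis plan cannot put it right: it cannot add identifiers to sheets that were gathered without them.

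**Working it through.** No figure in the Protocol rests on this point, so the check is mainly a reading of the sections against one another.

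**1. What the planned test needs.** Section 12.2 compares two means for secondary endpoints by Student's *t*-test or a Wilcoxon test, in the randomised arms. This is an unpaired comparison. It needs arm and visit on each sheet, but not patient identity. No paired-change or baseline-adjusted analysis of quality of life is planned.

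**2. What each way of marking the sheet would allow.**

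| Sheet carries | Unpaired comparison by arm at a visit | Within-patient change, baseline adjustment |
|---|---|---|
| No identifier | No | No |
| Visit only | No | No |
| Arm and visit, no patient code | Yes | No |
| Patient code and visit | Yes | Yes |

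**3. Which row the Protocol selects.** The literal sense of Section 4.5.2 points to the first or second row. The coding rule in Section 9.1.1 points to the last. No section says that the questionnaire bears a code, arm or visit label, and none says that it does not. The Appendix 4 and 5 items record that a sheet was handed out and collected, not its score or an identifier for it. The description of the database in Section 9.1.1 names no route for questionnaire answers.

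**4. Non-return.** Because the M3 and M6 forms carry the patient code next to the collection item, a missing sheet can be traced to a patient, and so to an arm, at those two visits. At inclusion it cannot be traced from Appendix 3, which has no such item.

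**5. The sample size is untouched.** Inputs from Section 12.1: difference 1, standard deviation 1.6, type I error 5% (two-sided, Section 12.2), power 80%.

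- n per group = 2 × (1.960 + 0.842)² × 1.6² / 1² = 40.2, rounded up to 41, or 82 in total, as stated.
- 41 × 1.2 = 49.2, which the Protocol takes to 50 per group, 100 in total.

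These concern HbA1c only and do not change.

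**6. For scale: what patient-level linkage could add.** Assume all 50 sheets per arm are returned, 80% power and a two-sided 5% level. The detectable standardised difference is (1.960 + 0.842) × √(2/50) × √(1 − r²), where r is the correlation between baseline and follow-up scores. The Protocol gives no such correlation, so the values of r are assumptions.

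| r | Detectable difference (SD) |
|---|---|
| 0 (no baseline used) | 0.56 |
| 0.3 | 0.53 |
| 0.5 | 0.49 |
| 0.7 | 0.40 |
| 0.8 | 0.34 |

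This is an opportunity that unlinked sheets would forgo. It is not the loss of a planned analysis.

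**The case against.** The strongest reply is that the whole point rests on one adjective. Section 9.1.1 already requires participant data to be coded and to show no names or addresses, so anonymous may mean no more than nameless. The sheets are completed at scheduled visits by known patients (Sections 5.2 and 5.3), where adding a code is natural, and labelling and data entry are often settled in data-management documents not shown here. A log form also need not repeat the scores of a separate instrument.

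Much of this stands, and it rules out three stronger readings that a reader might infer:

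- *The comparison is impossible, whatever is done.* The Protocol does not establish this. It nowhere says that sheets lack an arm, visit or code, and nameless sheets marked with arm and visit would support the unpaired test.
- *Non-response cannot be checked.* At M3 and M6 it can, from the coded forms.
- *A planned baseline-adjusted analysis would be lost.* Section 12.2 plans none for quality of life.

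What the reply does not remove is the conflict itself. If coded was meant, Section 4.5.2 says something else. Staff who took it at its word would break a link that no other section instructs them to keep.

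**Conclusion.** The point holds as a conflict in the Protocol's wording about how a secondary endpoint is collected. Section 4.5.2 is at odds with the between-group comparison in the Synopsis, the analysis by randomised arm in Section 12.2 and the coding rule in Section 9.1.1, and no route from answer to arm or visit is given.

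Its size depends on an assumption that the document leaves open. If the questionnaires are truly unmarked, the quality-of-life comparison by arm could not be made, and this would be irreversible after collection. If they are nameless but marked with arm and visit, the planned comparison stands, and only within-patient change and baseline adjustment are out of reach. HbA1c at 6 months and the sample size are unaffected on either reading. The correction is worth making before any sheet is handed out, because it is nearly free then and impossible afterwards.

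**What to change.** - In Section 4.5.2, replace anonymous with coded. State that each PedsQL sheet carries the existing inclusion number and the visit, with one label per visit throughout (V0, M3, M6). The Synopsis calls the inclusion visit V0 and Section 5.2 calls it V1.
- State that the scores enter the study database under that code, and bring the description of the database in Section 9.1.1 into line.
- Add to Appendix 3 the distribution and collection line that Appendices 4 and 5 already have.
- If the information leaflets call the questionnaire anonymous, change them to match.

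The cost is a label on each sheet, one line on a form and a few words of text; the code already exists. The small downside is that adolescents may answer slightly less freely on a coded sheet.
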